# Comparison of peri-implant submucosal microbiota in arches with zirconia or titanium implant-supported fixed complete dental prostheses: a study protocol for a randomized controlled trial

**DOI:** 10.1186/s13063-020-04853-7

**Published:** 2020-11-27

**Keywords:** Dental implants, Edentulous, Microbiota, Bio-complication, Zirconia, Titanium

## Abstract

**Background:**

The success rate of implant-supported prostheses for edentulous patients is relatively high. However, the incidence of biological complications, especially peri-implant mucositis and peri-implantitis, increases yearly after the placement of prostheses. The accumulation of pathogenic bacteria adjacent to a prosthesis is the main cause of biological complications. Titanium, one of the classical materials for implant-supported prostheses, performs well in terms of biocompatibility and ease of maintenance, but is still susceptible to biofilm formation. Zirconia, which has emerged as an appealing substitute, not only has comparable properties, but presents different surface properties that influence the adherence of oral bacteria. However, evidence of a direct effect on oral flora is limited. Therefore, the aim of the present study was to assess the effects of material properties on biofilm formation and composition.

**Methods:**

The proposed study is designed as a 5-year randomized controlled trial. We plan to enroll 44 edentulous (mandible) patients seeking full-arch, fixed, implant-supported prostheses. The participants will be randomly allocated to one of two groups: group 1, in which the participants will receive zirconia frameworks with ceramic veneering, or group 2, in which the participants will receive titanium frameworks with acrylic resin veneering. Ten follow-up examinations will be completed by the end of this 5-year trial. Mucosal conditions around the implants will be recorded every 6 months after restoration. Peri-implant submucosal plaque will be collected at each reexamination, and bacteria flora analysis will be performed with 16S rRNA gene sequencing technology in order to compare differences in microbial diversity between groups. One week before each visit, periodontal maintenance will be arranged. Each participant will receive an X-ray examination every 12 months as a key index to evaluate the marginal bone level around the implants.

**Discussion:**

The current study aims to explore the oral microbiology of patients following dental restoration with zirconia ceramic frameworks or titanium frameworks. The features of the microbiota and the mucosal condition around the two different materials will be evaluated and compared to determine whether zirconia is an appropriate material for fixed implant-supported prostheses for edentulous patients.

**Trial registration:**

International Clinical Trials Registry Platform (ICTRP) ChiCTR2000029470. Registered on 2 February 2020. http://www.chictr.org.cn/searchproj.aspx?

## Background

Full-arch fixed implant-supported prostheses have achieved satisfactory clinical results in edentulous patients with long-term implant survival of almost 100% [1]. However, biological complications after the placement of implant-supported fixed complete dental prostheses (IFCDPs) occur continuously over time [2]. Previous studies have indicated that peri-implant mucositis is associated with plaque accumulation [3, 4] around implants and prostheses and that the hygiene of IFCDPs could be influenced by the distance between the inserted implants in the jaw, the palatal extension of the prostheses [5], and the implant materials [6]. Investigations on the bacterial adhesion on titanium, the most commonly used materials in daily practice, have revealed that the corrosion of titanium increases plaque accumulation [7]. Zirconia ceramic frameworks, with or without ceramic veneering, is considered a promising material with good bio-compatibility and mechanical properties [8]. Therefore, many studies are currently investigating bacterial adhesion on zirconia discs/abutments as compared with titanium [9–12]. Results of in vitro studies suggest that zirconia is more resistant to bacterial colonization. However, in vivo evidence of bacterial control around implants remains controversial. For example, Grossner-Schreiber et al. [13] found that bacterial counts were higher with titanium discs than zirconia, while Scarano et al. [14] showed that bacterial adhesion was significantly higher with pure titanium surfaces as compared with zirconium oxide surfaces and Egawa et al. [15] found that bacterial adherence to titanium was comparable to that of zirconia if the surfaces of both materials had mirror-like flat textures.

These discrepancies may be due to differences in study design. First, material surface roughness is a key factor for bacterial colonization [16, 17]. Therefore, statistical analyses of bacterial adhesion on materials without uniform surface roughness are not comparable [9–11, 14]. Second, studies that included patients with partial edentulism could not exclude the influence of the oral flora on the remaining teeth on the establishment of peri-implant microbiota, which might have influenced comparisons of peri-implant microbiota between different groups [12–14]. To eliminate such interfering factors, full-arch restoration with materials with equal smoothness should be investigated. A previous study of 20 edentulous investigated early material colonization around zirconia vs. titanium abutments before final restorations found no difference in early bacterial colonization between the two materials. Since this observation period was relatively short (3 months) [10], additional studies are needed to determine whether there are differences in the performance of frameworks after final restoration. Considering that bacterial colonization might be influenced by aging of zirconia [18] and long-term corrosion of titanium [7], a comparative study with a longer observation period is warranted.

Therefore, there is a need for a randomized controlled study with a sufficient sample size and long-term observation period to provide direct clinical evidence about the effect of the surface properties of full-arch implant-based prostheses on submucosal microbiota. The aim of the current study is to compare the clinical conditions and peri-implant microbiota of edentulous patients following dental restoration with titanium-based vs. zirconia-based prostheses.

## Objectives

The aims of the study are (1) to investigate and compare the implant survival and biological complication rates between two different restorative materials on full-arch fixed implant-supported rehabilitation and (2) to compare the effect of two different restorative materials on the diversity of microbiota colonizing full-arch fixed implant-supported restorations (i.e., zirconia frameworks with ceramic veneering vs. titanium frameworks with acrylic resin veneering).

## Methods and study design

### Study design and setting

The proposed study is designed as a pragmatic randomized controlled trial with a 5-year follow-up period. A Consolidated Standards of Reporting Trials diagram is presented in Fig. 1. We plan to enroll 44 edentulous patients (mandible) in need of dental implant-based prostheses. The goal of the treatment protocol is to rehabilitate these patients with full-arch fixed implant-supported prostheses with placement of 4–6 titanium implants in the mandible. The patients will be randomly assigned to receive restorative materials of zirconia frameworks with ceramic veneering (Fig. 2) or titanium frameworks with acrylic resin veneering (Fig. 3). Both groups will receive titanium implants with sandblasted, large grid, and acid-etched surfaces. The trial will last for 5 years, and the patients will be followed up at 6-month intervals. During each visit, the patient will undergo a clinical examination, surface roughness test, and submucosa plaque collection, while biological and mechanical complications will be treated. One week before each visit, the patient will receive periodontal maintenance, including ultrasonic debridement using an ultrasonic device with polyetheretherketone-coated tips (AIRFLOW® Prophylaxis Master; EMS Dental, Nyon, Switzerland) combined with erythritol air-polishing (AIR-FLOW® handy 3.0 PERIO; EMS Dental). X-ray assessment will be performed yearly. A treatment timeline is shown in Table 1.

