### Interventions

The aim of the treatment protocol is to rehabilitate these patients with full-arch fixed implant-supported prosthesis with placement of 4–6 implants in the mandible. Patients will be randomly assigned to receive one of two restorative materials: zirconia ceramic frameworks with or without ceramic veneering vs. titanium frameworks with acrylic resin veneering. Before prosthesis fitting, the patients will undergo a standard polishing procedure (GB/T 6060.2-2006) and examination to ensure the same surface roughness between groups. The surface roughness of all specimens will be measured with the use of a profilometer (Mitutoyo Surftest SJ-401; Mitutoyo Corporation, Kawasaki, Japan), as described in a previous study [19]. The implant number, implant site, implant diameter, implant length, implant torque, distances between the inserted implants, and shapes of the intaglio surface will be recorded as basic information.

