### Randomization, allocation, and blinding

The subjects will be randomly allocated to one of two groups according to the prosthetic materials: titanium framework with acrylic resin veneering (group 1) or zirconia framework with/without ceramic veneering (group 2). The allocation of patients will be randomized using computer-generated permuted block randomization with an allocation ratio of 1:1. Randomization will be performed by sealed envelopes that will be opened after final impressions are obtained.

Microbiota analysis will be blinded after assignment to the intervention groups. Each sample will have a number associated with an allocation sequence, as well as information pertaining to the dental position and acquisition time. The technician conducting the PCR analysis will be blinded to the source of the sample. Interim statistical analysis will be performed at 1 and 3 years after implantation of the final prostheses. Final statistical analysis will be conducted at the end of the trial with the analyst blinded to both patient allocation and the interim analysis results.

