#### Clinical monitoring and X-ray assessment

Continuous variables will be described as the mean ± standard deviation or median. Grade and qualitative data will be described as a percentage. Age and other basic information between groups will be compared with the independent *t* test. Gender, implant survival rates, peri-implantitis rates, and peri-implant mucositis rates between the test and control groups will be compared using the chi-square test. PD and X-ray indices between groups will be compared using the independent *t* test. The differences in PLI and BI between the two groups will be evaluated, as well as the differences in PLI and BI over a period of 10 follow-ups. A generalized estimating equation will be used to eliminate possible internal correlations between multiple implants of the same patient. A Cox regression model will be used to exclude the influences of the shapes of the intaglio surface, the distances between the inserted implants, and other cofounders affecting the primary and secondary outcome variables. A probability (*p*) value of < 0.05 will be considered statistically significant.

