#### Microbiological monitoring

The mean counts (× 10^5^) of individual bacterial species and the percentage of the total DNA probe will be calculated initially for each implant, then per subject and averaged across patients between groups. Periodontal pathogens include *P. gingivalis*, *Fusobacterium nucleatum* subspecies, and *P. intermedia*, among others. The proportions for the species will be distributed into the six complexes and an “other” group, as proposed by Socransky et al. [27]. Differences in microbiological parameters between groups will be identified using the Wilcoxon signed-rank test. Adjustments for multiple comparisons [28] will be performed when the bacterial species are evaluated simultaneously. The level of significance will be set at 5%.

Alpha and beta diversity analyses will be performed using Primer7 software and the QIIME2 microbiome bioinformatics platform [29, 30]. Alpha diversity, Shannon’s diversity index of both species number and distribution, Margalef’s index of numbers, and Pielou’s index of evenness of distribution [31–33] will be analyzed, and the significance of the differences between groups will be derived using the unpaired Student’s *t* test. Beta diversity analysis includes visualization of data at multiple taxonomic levels, with unweighted and weighted UniFrac distance metrics in order to generate PCoA plots [34]. Analysis of similarity (ANOSIM) will be performed to determine whether there are significant differences in microbial communities between groups. White’s non-parametric test will be applied to test for differences in the abundance of specific microbiota between the groups, with a false discovery rate cutoff of 0.005 with the use of STAMP [35].

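### The full-arch design is justified as eliminating the influence of remaining teeth, but only the mandible must be edentulous, and the planned microbiota tests make no allowance for upper teeth

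*Protocol article*

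**What the plan says.** **Rationale.** The Background argues that "studies that included patients with partial edentulism could not exclude the influence of the oral flora on the remaining teeth", and that this may have affected comparisons between groups. Its answer is: "To eliminate such interfering factors, full-arch restoration with materials with equal smoothness should be investigated".

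**Population.** The abstract's Methods paragraph says "We plan to enroll 44 edentulous (mandible) patients seeking full-arch, fixed, implant-supported prostheses". Study design and setting says "We plan to enroll 44 edentulous patients (mandible) in need of dental implant-based prostheses". The inclusion criterion under Recruitment asks for an edentulous jaw, in the singular. Neither the inclusion nor the exclusion list mentions the maxilla or upper teeth. The list excludes uncontrolled periodontitis only.

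**Allocation.** "The allocation of patients will be randomized using computer-generated permuted block randomization with an allocation ratio of 1:1". No stratification factor is named.

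**Recorded baseline items.** The Interventions section lists implant and prosthesis features, ending with "distances between the inserted implants, and shapes of the intaglio surface will be recorded as basic information".

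**Adjustment.** The clinical and X-ray analysis plans a Cox model to remove the influence of intaglio shape, "the distances between the inserted implants, and other cofounders affecting the primary and secondary outcome variables".

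**Microbiota analysis.** For the alpha-diversity indices, "the significance of the differences between groups will be derived using the unpaired Student’s *t* test". Beta diversity is compared by ANOSIM, and species by Wilcoxon and White's tests. No covariate or stratum appears in any of them. Diversity of submucosal species is listed among the primary outcomes.

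**The concern.** The protocol singles out one factor, flora from remaining teeth, as a reason why earlier comparisons of materials are hard to interpret, and offers its own design as the answer. A full-arch lower prosthesis removes teeth from the restored arch. It does not remove them from the mouth of a patient who keeps upper teeth. If such patients enter, the factor is still present in the trial, and the tests for a primary outcome take no account of it.

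Two things are at stake. The first is precision and chance imbalance in a trial of 22 per arm. The second is interpretation: a reader of the results would take the Background to mean that dental flora had been designed out, and the entry criteria do not ensure that.

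**Working it through.** The main point needs no arithmetic.

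| Question | Where the protocol answers | Answer |
|---|---|---|
| Is flora from remaining teeth a concern? | Background | Yes, and the design is meant to eliminate it |
| Must the upper arch be edentulous? | Abstract; Study design and setting; Recruitment | No; only the mandible or jaw |
| Is upper-arch status named as recorded? | Interventions | No |
| Is it a stratum? | Randomization, allocation, and blinding | None named |
| Is it a covariate for clinical outcomes? | Clinical monitoring and X-ray assessment | Not named; an open-ended reference to other confounders |
| Is it a covariate for diversity? | Microbiological monitoring | No; two-group tests |

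The open-ended reference does not close the gap for diversity. It belongs to a Cox model, which analyses time to an event, whereas Shannon, Margalef and Pielou indices and UniFrac distances are not event times.

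**Size of chance imbalance (illustration).** The protocol gives no figure to reproduce here. Inputs: 44 patients, 22 per arm (Sample size). Assumption: K of the 44 have upper teeth. If upper-arch status is unrelated to enrolment order, the number X in one arm is hypergeometric:

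P(X = x) = C(K, x) · C(44 − K, 22 − x) / C(44, 22), and the difference between arms is |2X − K| patients.

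| Assumed K of 44 (share) | Difference | P |
|---|---|---|
| 9 (20%) | 5 or more patients (5/22 = 23 points) | 0.132 |
| 13 (30%) | 5 or more (23 points) | 0.185 |
| 22 (50%) | 4 or more (4/22 = 18 points) | 0.366 |
| 22 (50%) | 6 or more (6/22 = 27 points) | 0.131 |
| 22 (50%) | 8 or more (8/22 = 36 points) | 0.034 |
| 31 (70%) | 5 or more (23 points) | 0.185 |

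The difference always has the same parity as K, so the cut-offs move in steps of two patients. Over every K from 9 to 31, the chance of a gap of at least 20 points runs from 0.07 to 0.23, and of at least 30 points from 0.01 to 0.07. With the 36 patients that Recruitment expects (18 per arm) and half with upper teeth, a gap of four or more (4/18 = 22 points) has probability 0.318.

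**What an imbalance would do.** Let upper teeth shift an outcome by δ within-stratum SDs. The documents give no δ; take 0.5 to 1 as an assumed range.

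- Shift in the between-arm difference = δ × imbalance. With 4/22 = 0.18 this is 0.09 to 0.18 SD. The standard error of the difference is √(2/22) = 0.30 SD, so the shift is 0.3 to 0.6 standard errors. With 6/22 = 0.27 it is 0.14 to 0.27 SD, or 0.45 to 0.9 standard errors.
- Variance of an unadjusted comparison is multiplied by about 1 + p(1 − p)δ². At p = 0.5 this is 1 + 0.25 × 0.25 = 1.06 to 1 + 0.25 × 1 = 1.25.

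**The case against.** - **Same-arch reading.** The Background can be read as concerning teeth in the restored arch, which a full-arch prosthesis does remove, and it says only that remaining teeth might have influenced comparisons. This is fair. But the passage sets no arch limit, and the limit should be stated if it is meant.
- **A stronger reading of that passage.** A reader might infer that the protocol treats upper-arch status as a main determinant of the microbiota. It does not say so.
- **Who will enter.** A reader might infer that patients with upper teeth will be enrolled. The text permits it but does not say so. The exclusion of uncontrolled periodontitis fits a population with some teeth, but it may be a generic item and proves little.
- **Recording and adjustment.** Age and gender are compared between groups but are absent from the Interventions list, so that list is not the whole baseline dataset, and upper-arch status may be recorded. The reference to other confounders could cover it for clinical outcomes. It would therefore be wrong to say that the factor is certainly unrecorded or unadjusted; it is not named. This does not rescue the diversity tests, which are stated without any covariate.
- **Randomisation.** Upper-arch status is fixed before allocation, so it causes no systematic bias, and the type I error of an unadjusted test already allows for chance imbalance. That stands. Any unstratified prognostic factor in a trial of 44 shares the problem; this one is different only because the protocol itself names it as an interfering factor.
- **Magnitude.** The probabilities rest on assumed prevalence, and no effect of upper teeth on any outcome is given. They show how often arms could differ, not that a result would change.

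**Conclusion.** The point holds in a limited form. The stated rationale, to eliminate the influence of remaining teeth, is not delivered by entry criteria that address only the lower arch, and the tests for diversity, a primary outcome, are specified without allowance for the factor. The randomised comparison remains valid. What is lost is some precision, protection against chance imbalance, and support for the claim that dental flora has been removed.

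The size is modest and conditional. For an assumed 20% to 70% of patients with upper teeth, a gap of 20 points or more between arms has a probability of roughly 7% to 23%. The documents do not support the inference that the material comparison would be biased or uninterpretable.

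**What to change.** 1. Record upper-arch status (natural teeth present versus none) from the clinical and radiographic assessment already done before implant surgery, and fix it at baseline. It should be retrievable for patients already enrolled.
2. Prespecify it as a covariate for all patients:
   - in the generalized estimating equation models for PLI and BI;
   - in a regression model for the alpha-diversity indices, in place of the unpaired t test;
   - in a covariate-capable distance-based permutation test for beta diversity (for example PERMANOVA with patients as the permuted units), in place of ANOSIM, which takes no covariate as planned.
3. Limit the Background statement either to teeth in the restored arch or to patients without upper teeth. If the second is chosen, give the number of such patients; on a 50% assumption it would be about 22 of 44.

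Stratifying the permuted blocks for patients not yet allocated is optional. Recruitment began in May 2020, so strata would cover only part of the sample and would need a second envelope series. The covariate covers everyone.

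The cost is one baseline field and one degree of freedom per model, with no new procedure for patients.

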**Fig. 1 Fig1:**
[figure not shown]
Consolidated Standards of Reporting Trials diagram

**Fig. 2 Fig2:**
[figure not shown]
Zirconia framework with ceramic veneering (group 1). **a** Zirconia framework. **b** Zirconia framework with ceramic veneering

**Fig. 3 Fig3:**
[figure not shown]
Titanium framework with acrylic resin veneering (group 2). **a** Titanium framework. **b** Titanium framework with acrylic resin veneering

**Table 1 Tab1:** Participant timeline

TIMEPOINT	T0	T1	T2	Month0	1 week before Month 6	Month6	1 week before Month 12	Month12	1 week before Month 18	Month18	1 week before Month 24	Month24	1 week before Month 30	Month30	1 week before Month 36	Month36	1 week before Month 42	Month 42	1 week before Month 48	Month 48	1 week before Month 54	Month 54	1 week before Month 60	Month 60
**ENROLMENT:**																								
**Eligibility screen**	X																							
**Informed consent**	X																							
**Implant surgery**		X																						
**Impression**			X																					
**Allocation**				X																				
**INTERVENTIONS:**																								
**Final restoration:** **titanium**				X																				
**Final restoration:** **zirconia**				X																				
**MAINTANENCES:** **Ultrasonic debridement with PEEK tips**					X		X		X		X		X		X		X		X		X		X	
